##### Assessment of Hypoxic Cerebral Injury

Assessment of hypoxic cerebral injury is primarily based on the combination of clinical signs, serum neuron-specific enolase concentrations, and neurophysiological examination of somatosensory evoked potentials. Other examinations, for example, magnetic resonance imaging, are performed when required. The evaluation of potential hypoxic cerebral injury is usually initiated on the third or fourth day after CA.

##### Intensive Care Unit Procedures

Airway suction is routinely performed once daily to secure patent airway and as needed if there are signs of excessive airway secretions. Airway suction is performed with a 10, 12, or 14 French scale catheter (depending on endotracheal tube size) through a closed suction system.

Shift of position is routinely performed every third hour.

Spontaneous breathing trials (SBTs) are considered in patients who have spontaneous respiration, airway patency, reversal of the cause of respiratory failure, no uncontrolled infection or metabolic disturbance, heart rate <120, systolic BP 90-180 mm Hg, oxygen saturation >90%, FiO_2_ <0.5, and positive end-expiratory pressure (PEEP) ≤8 cmH_2_ O. The SBT is performed using pressure-supported ventilation with inspiratory pressure support of approximately 8 cmH_2_ O and PEEP 6-8 cmH_2_ O for 10-30 min.

### Study Procedure

#### Screening and Recruitment

Patients will be screened for eligibility and recruited at the time they are admitted to the ICU or CCU for intensive care after OHCA (Figure 1).

Demographic and clinical data will be extracted from the patient’s medical records and documentation from emergency medical service (EMS) personnel involved in the treatment of CA. Registrations of clinical variables, as part of routine critical care from the time of ICU/CCU arrival until inclusion, will be used.

If there is no contraindication to insert a pulmonary artery catheter (PAC), the catheter is inserted as early as possible after inclusion.

#### Baseline Variables

At time of inclusion the following variables will be registered:

Patient characteristics: age, sex, ethnicity, weight, height, and premorbid cerebral performance category (CPC) [27,28]Charlson Comorbidity Index [29]Characteristics related to the CA (*Utstein Style Template*) [30]: location, witnessed arrest, time of emergency call, bystander CPR, time of EMS personnel arrival, initial monitored rhythm, time to first defibrillation, time to ROSC, presumed cardiac or noncardiac etiology, and medications given during or after CPR. End-tidal CO_2_ results, if appliedTemperature at admissionKnown pulmonary aspiration during CPRInterventions

#### Registrations During the Study Period

Clinical data are registered in the electronic ICU chart, Picis Critical Care Manager (Optum Inc, USA). After inclusion, the following variables will be recorded:

At the time of inclusion and every minute:

Basic vital measurements: heart rate and rhythm, invasive arterial blood pressure, pulmonary artery pressure, mixed venous oxygen saturation (SvO_2_, calibrated twice daily), central venous blood pressure, peripheral transcutaneous oxygen saturation, and temperatureCentral hemodynamic measurements: CO and systemic vascular resistance (SVR), and corresponding indexed values (related to body-surface area)Respiratory support: ventilator mode, respiratory rate, FiO_2_, minute ventilation, PEEP, and plateau pressure

At the time of inclusion and every following hour:

Fluid balance: fluid administrations, transfusions, and urine outputAll medications

At the time of inclusion and every sixth hour:

Arterial blood gas analysis, including electrolytesMAAS score

After 24 hours:

Simplified acute physiology score (SAPS) II [31]

At the time of inclusion and twice daily:

Pulmonary artery occlusion pressureCentral venous and mixed venous blood gas

At the time of inclusion and daily:

Standardized echocardiographic evaluation performed by a trained cardiologistIntra-abdominal pressureClinical chemistry: white blood count, thrombocyte count, creatinine, blood urea nitrogen, C-reactive protein, troponin-T, probrain natriuretic peptide, bilirubin, albumin, and haptoglobinBlood samples for inflammatory and endothelial biomarkersModified clinical pulmonary infection score (CPIS) [32]Sequential organ failure assessment (SOFA) score [33]Glasgow Coma Score [34]Percutaneous coronary intervention, dialysis, and/or aorta balloon pumpResults from chest x-ray or other diagnostic imaging tools ordered during the hospital stayOther events during the study period (eg, arrhythmias and seizures)

**Figure 1 figure1:**
[figure not shown]
Flowchart summarizing patient enrollment and main study procedures. OHCA: out-of-hospital cardiac arrest; ROSC: return of spontaneous circulation; CCU: coronary care unit; ICU: intensive care unit; CA: cardiac arrest; PAC: pulmonary artery catheter; PAOP: pulmonary artery occlusion pressure; CPC: cerebral performance category.

#### Biomarkers

As part of the study, we will establish a biobank for analysis of inflammatory and endothelial biomarkers. Blood samples will be taken at inclusion and every morning the 5 following days. After gentle mixing, the blood samples are placed vertical for 30 min in ambient temperature, and then centrifuged at 2200 g for 10 min. The supernatants are stored at −80°C within 1 hour from the time of sampling. During the study period, additional full blood will be drawn and stored at −80°C.

We will analyze the following biomarkers: interleukin (IL)-1β, IL-1 receptor antagonist (IL1-ra), IL-2, IL-4, IL-5, IL-6, IL-7, IL-8, IL-9, IL-10, IL-12 (p70), IL-13, IL-15, IL-17, eotaxin, basic fibroblast growth factor, granulocyte-colony stimulating factor, granulocyte macrophage colony stimulating factor, interferon γ, interferon-inducible protein 10, monocyte chemotactic protein 1, macrophage inflammatory protein 1α and 1β, platelet derived growth factor-BB, regulated upon activation T cell expressed and secreted, tumor necrosis factor, vascular endothelial growth factor, syndecan-1, sE-selectin, heparan sulfate, hyaluronic acid, soluble trombomodulin, and sVE-cadherin. Other biomarkers of interest, identified later, may be included in the final analysis.

#### Follow-Up After Discharge From Hospital

Follow-up after discharge from the hospital will include the following:

ICU length of stay.Hospital length of stay.Survival status at hospital discharge and after 6 months.CPC at hospital discharge and after 6 months.

### Ethical Considerations

Research on critically ill patients, who are sedated or comatose and, therefore, not able to provide consent, calls for special ethical considerations. For the study, it is vital that clinical information is obtained from the initial critical stage of the disease. This study will not increase the overall risk for the patients, and the study is justifiable according to the *World Medical Association’s Declaration of Helsinki* regarding *Ethical Principles for Medical Research Involving Human Subjects*, June 1964, and its later amendments [35]. We will include patients in the study when they are admitted to the ICU/CCU and at the earliest feasible moment ask for consent from their relatives. Patients, who regain competency to give an informed consent, will later be asked for a deferred consent. This procedure is approved by the Regional Committee for Medical and Health Research Ethics, Central-Norway Health Region (REK Midt, No. 2015/1807).

### Assessment of Safety

Besides establishing and calibrating PAC (Swan-Ganz CCOmbo, Edward Lifescience, USA) and drawing blood for analysis of inflammatory biomarkers at a maximum of 5 time points, the study does not involve other interventions differing from routine care after OHCA. The insertion of PAC induces some benefits and some risks. One of the benefits is the potential of improved circulatory monitoring and support, including a more precise administration of fluids and vasoactive medications. However, complications related to the placement of PAC have also been reported. In a Cochrane report, PAC was neither found to increase mortality or length of stay in the ICU or the hospital (high-quality evidence according to the Grading of Recommendations Assessment, Development and Evaluation (GRADE) system for both the findings). The Acute Decompensated Heart Failure Syndromes Registry compared 502 patients with decompensated heart failure and PAC with 502 controls [36] and observed that the risk of all-cause death was lower in the PAC group than the control group (hazard ratio 0.3, 95% confidence interval (CI) 0.13-0.7). In a large study from Leipzig where 3730 patients with PAC who underwent cardiac surgery, only 0.1% experienced serious complications [37], a similar rate as transesophageal echocardiography (0.2%) [38]. The nursing-staff at ICU and CCU are trained in PAC care and extra lectures in PAC use will be given before and during the study. Only doctors, competent of PAC use, will perform measurements of pulmonary artery wedge pressure. We believe that the patients included will experience neither benefit nor harm by participating in this study.

### Statistical Analysis Plan

#### Statistical Methods

Descriptive data are presented with either median or interquartile range, or mean with 95% CI, as appropriate. For missing observation of physiological variables (eg, blood pressure), a value corresponding to the mean of the observation before and after this time point will be applied. For biomarkers, the value 0 is attributed if a result is below the detection limits of the assay. Statistical analyses will be performed using Stata or R.

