#### Circulatory State Transitions During Post Cardiac Arrest Syndrome

During critical illness, most patients go through different states of hemodynamic stability. We have categorized the circulatory state after CA in 3 different categories based on data obtained from routine care (Table 1). Every 10 min, a patient is classified according to the least favorable measurement at that time (eg, isolated MAP of 40 mm Hg is sufficient to classify a patient to have severely disturbed circulation).

We will validate the appropriateness of the defined categories against the cardiac index.

Patients may go back and forth between the clinical states, defined in Table 1, corresponding to the severity of their illness and its progression (Figure 2), and the changes from one clinical state to another will be recorded. By using survival analysis methodology, we allow for right censoring, which means that the information from patients with limited follow-up time can be included in the analyses. A patient who is in a certain clinical state at time *t* might remain in the same state or change to one of 2 others at time *t* +1. In such multi-endpoint settings, the clinical states compete with each other, and the transitions over time are best studied with methods developed for competing risk analyses.

**Table 1 table1:** Circulatory states.

Variables	Circulation		
	Undisturbed	Disturbed	Severely disturbed
Mean arterial pressure, mm Hg	≥65	45-64	<45
Heart rate, bpm	51-100	<50, 101-130	≤40, >130
Lactate, mmol/L	<2	2–4	>4
ScvO_2_, %	≥65	50-64	<50
Fluid resuscitation, L/hours	<0.5	0.5-1.9	≥2
Norepinephrine, μg·kg^−1^·min^−1^	<0.1	0.1-0.29	≥0.3
Dobutamine, μg·kg^−1^·min^−1^	No	<10	≥10
Vasopressin	No	No	Yes
Epinephrine	No	No	Yes
Levosimedan	No	No	Yes
Aorta balloon pump	No	No	Yes

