#### Patterns Predictive of Deterioration in Circulatory State

We anticipate that not all patients will follow the same circulatory trajectory; during the study, some will deteriorate and some will improve in circulatory status, and during our observation, many will have several state transitions. We plan to analyze events before deteriorations to identify patterns of circulatory and inflammatory response measurements predictive of clinical state deteriorations. These patterns will be compared with those in patients who improve their circulatory status or remain unchanged.

To explore the predictive value of previous measurements to foresee a clinical deterioration, we will use 2 different approaches. The outcome variable will be dichotomized to deterioration versus no deterioration (status quo or improvement). First, we will test different timelags between measurements and deteriorations to see which is more informative (eg, 1 hour, 2 hours, 3 hours). For this analytic approach, we will use univariable and multivariable logistic regression. Second, we will use methods from survival analysis to assess continuous alterations in covariates on the outcome. For this analysis, we will use Aalen’s linear model, which is an intensity regression model. Variables from the 2 groups will also be explored in respect to its relation to mortality and CPC at discharge from hospital.

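### Filling gaps with the mean of the observations before and after puts later values into states and predictors; serious for long gaps, and for lactate and ScvO2 if slots between samples are filled this way

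*Protocol article*

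**What the plan says.** The protocol article gives one filling rule for physiological variables, with blood pressure as its example: "a value corresponding to the mean of the observation before and after this time point will be applied" (Statistical Methods). Biomarkers have a separate rule, which covers only results below the detection limit.

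The section on circulatory state transitions builds the outcome from such variables: "Every 10 min, a patient is classified according to the least favorable measurement at that time". Table 1 lists eleven state-defining variables, among them mean arterial pressure, heart rate, lactate and ScvO2.

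Registrations During the Study Period sets the recording intervals. Pressure and heart rate are recorded every minute. For arterial blood gases the schedule is "At the time of inclusion and every sixth hour", and for central venous blood gases "At the time of inclusion and twice daily".

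Patterns Predictive of Deterioration in Circulatory State then relates earlier measurements to later worsening of the state: "First, we will test different timelags between measurements and deteriorations to see which is more informative", with 1, 2 and 3 hours as examples. Logistic regression is used for the lags, and Aalen's linear intensity model for covariates that change over time. The Discussion (Rationale for This Study) announces a prediction model built on the findings.

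**The concern.** A predictor dated at time t may use only what was known at time t. A value filled with the mean of its two neighbours is half an observation that did not yet exist. If that later observation also helps to define the later state, the predictor contains part of its own outcome. Covariates in an intensity model must likewise depend only on the past, and this fill breaks that condition.

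Three results are at stake:
- the apparent strength of predictors;
- the comparison of lags, because shorter lags are contaminated more often;
- the states themselves, because a filled value can place a patient in a worse category before any abnormal value was measured.

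A cohort of 50 patients at one centre gives little chance of exposing a falsely strong predictor.

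**Working it through.** The plan states no figure that depends on this point, so there is none to reproduce. The planned 50 patients rest on no formal calculation.

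**Inputs from the article.** State grid 10 min; vital signs every minute; arterial gas every 6 h; central venous gas twice daily (12 h apart); lags 1, 2 and 3 h; Table 1 cut-offs.

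**Assumptions.** Lactate comes from the arterial gas and ScvO2 from the central venous gas. The 10-min slots between scheduled samples count as missing. The article states neither.

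**1. Effect on states.** Fill = (previous + next) / 2.
- Lactate 1.5 then 4.5 mmol/L: (1.5 + 4.5) / 2 = 3.0, in the disturbed band (2–4). The patient enters it 10 min after a normal sample, 5 h 50 min before the abnormal one.
- MAP 70 then 40 mm Hg: 55, in the disturbed band (45–64), an intermediate state set by the later value.
- MAP 75 then 58 mm Hg: 66.5, still undisturbed. So the fill does not always move the state.

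**2. Effect on lagged predictors.** Let a sampling gap have G slots: 36 for 6 h, 72 for 12 h. Without a scheduled value are 35 of 36 lactate slots and 71 of 72 ScvO2 slots. A predictor in slot k has its outcome at k + 6L for a lag of L hours. The next sample is at slot G. The fill contains a value taken at or after the outcome time when k ≤ G − 6L, so the share is (G − 6L) / G.

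| Lag | Lactate (G = 36) | ScvO2 (G = 72) |
|---|---|---|
| 1 h | 30/36 = 83% | 66/72 = 92% |
| 2 h | 24/36 = 67% | 60/72 = 83% |
| 3 h | 18/36 = 50% | 54/72 = 75% |

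The share falls as the lag grows, which favours short lags. In the other 6L − 1 filled slots (5, 11 and 17) the fill contains a sample taken after its nominal time but before the outcome, so the true lag is shorter than its label.

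**3. Minute-recorded signals.** One missing minute reaches 1 min ahead, against lags of 60, 120 and 180 min. A lagged predictor takes in a value from the outcome time or later only if the missing run is at least about as long as the lag.

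**4. Illustration of size.** For successive standardised measurements with correlation ρ, the fill correlates √((1 + ρ)/2) with the later one. At ρ = 0 this is √0.5 = 0.71, where the last observed value correlates 0. In 400,000 simulated pairs, the AUC for the next value exceeding the median was:

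| ρ (assumed) | Last value | Two-sided mean |
|---|---|---|
| 0 | 0.50 | 0.83 |
| 0.3 | 0.64 | 0.89 |
| 0.6 | 0.78 | 0.94 |
| 0.8 | 0.88 | 0.97 |

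A second simulation assumed log-normal lactate (median 2.5, log SD 0.5) with a first sample of 4 or below. The AUC for the next sample exceeding 4 was 0.50 against 0.96 with independent samples, and 0.85 against 0.99 with tracking (log-change SD 0.35).

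**5. End of follow-up.** After the last observation before death or other censoring there is no later value, so the rule gives nothing there.

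**The case against.** A missing observation most naturally means a recording that was due and is absent. No gas was due in the slots between scheduled samples, and the article does not say that they are interpolated. How sparse variables are held between samples may be settled in a fuller document that is not shown. This stands, and it makes the slot percentages conditional. A reader might infer that nearly all lactate and ScvO2 slots will certainly be filled with future values; the text does not support that.

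For the article's own example, blood pressure, isolated gaps do almost no harm at the planned lags. That stands too. A reader might infer that all states and predictors are contaminated. Only filled values are, no missingness rate is given, and the inflammatory and endothelial biomarkers fall under a different rule.

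The simulations predict one variable from a mean that contains it. The planned outcome is worsening of a state set by the worst of eleven variables, and lactate drives it only when nothing else is as bad or worse. Moreover, if the fill also defines the state, some events are moved forward: in the log-normal simulation, 34% (independent) and 52% (tracking) of the later values above 4 were already classed as severe by the fill. For the remaining events the AUC of the fill was still 0.94 and 0.97. Leakage therefore persists, but the figures do not estimate its size in this study.

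Finally, it is tempting to argue that past-only filling would give the right transition times. It would not: it ties lactate and ScvO2 transitions to the sampling schedule and can date a true crossing late. The case against the two-sided mean rests on look-ahead, not on better timing.

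None of this removes the core point. The rule is stated, two-sided and unlimited in gap length, and nothing in the article restricts it in the transition or prediction analyses.

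**Conclusion.** The point holds in limited form. Followed as written, the rule gives filled values that are not earlier measurements, which conflicts with the prediction aim and with both planned models.

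- Isolated gaps in minute-recorded pressure or heart rate: negligible at lags of 1 to 3 h.
- Gaps in any variable at least as long as the lag: serious, frequency unknown.
- Lactate and ScvO2: serious if the slots between samples are filled by this rule. The shares of 50–83% and 75–92% rest on that reading and on the assumed sources and schedule. Extra clinical gases would shorten the gaps.

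The rise in AUC from 0.50 to 0.96 with no true predictability shows that the mechanism can be strong, no more. The study is exploratory and the rule can be changed before analysis without touching data collection. It should be corrected before states are derived, but it does not undermine the study as designed.

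**What to change.** For state classification and for every predictor in the transition and prediction analyses, replace the two-sided mean with a past-only fill: carry the last observation forward up to a stated maximum age (for example, one scheduled interval per variable), then treat it as missing. State that this also governs lactate and ScvO2 between samples. Keep the two-sided mean for descriptive plots only. Add a sensitivity analysis with states built without lactate and ScvO2.

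The cost is a sentence or two in the plan and some reprogramming, with no change to data collection. The downside should be stated openly. Carried-forward values can be up to one sampling interval old, and transitions driven by lactate or ScvO2 are dated when detected, up to about 6 h or 12 h after the true crossing. They should be reported as detection times.

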### Sample Size

This is an observational study, and the frequency of abnormal biomarkers, circulatory states, and endpoints are largely unknown; therefore, no formal sample size calculation has been performed [24]. On the basis of a sample size from similar studies describing pathophysiology, we aim at including 50 patients [21,25].

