#### Relation Between Distributive Shock and Inflammatory Biomarkers

We will study the relationship between alterations in inflammatory and endothelial biomarkers and the changes in SVR, in CO, and the need for fluid replacement. As described above, patients with hypotension and low SVR will be treated with norepinephrine. Therefore, we will analyze potential independent biomarkers and other predictors of SVR adjusted for a dose of norepinephrine.

Vasoplegia might also occur as part of an infection, and CA patients are prone to aspiration and pneumonia after CPR. Therefore, we will calculate modified CPIS daily to describe how many patients develop clinical pneumonia.

Circulatory failure might also be due to structural heart defects (eg, mitral valve insufficiency). An experienced cardiologist will perform echocardiogram daily to assess the heart’s function.

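### Coding every biomarker result below the detection limit as 0 is a poor fixed rule: for markers with many non-detects it biases means, exaggerates changes across the limit and leaves log-scale results arbitrary

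*Protocol article*

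**What the plan says.** The Statistical Methods section fixes the rule for all biomarkers: "For biomarkers, the value 0 is attributed if a result is below the detection limits of the assay". It makes no distinction between markers, sets no condition on the share of non-detects, and names no sensitivity analysis. For summaries, the same section says "Descriptive data are presented with either median or interquartile range, or mean with 95% CI, as appropriate", so both medians and means are allowed.

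The Biomarkers section lists the panel, beginning "We will analyze the following biomarkers: interleukin (IL)-1β, IL-1 receptor antagonist (IL1-ra), IL-2, IL-4, IL-5, IL-6". By count it has 33 markers: 27 cytokines, chemokines and growth factors, and 6 endothelial markers. They are used in three places:

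- The section on distributive shock relates changes to changes: "We will study the relationship between alterations in inflammatory and endothelial biomarkers and the changes in SVR, in CO", and also to fluid need.
- The same section models SVR: "we will analyze potential independent biomarkers and other predictors of SVR adjusted for a dose of norepinephrine".
- The section on patterns predictive of deterioration uses inflammatory measurements as predictors: "For this analytic approach, we will use univariable and multivariable logistic regression", followed by Aalen's linear model.

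No log transformation, or any other biomarker scale, is stated.

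**The concern.** A non-detect is a left-censored value: it is known to lie in an interval, and 0 is the lowest point of that interval. The plan allows for right censoring of follow-up time but discards the equivalent information for concentrations. The third and fourth research questions depend on the biomarkers, so for markers often below the limit the results could reflect the coding and the assay's limit as well as the biology. Skewed concentrations are often analysed as logs or ratios, and the rule leaves no usable value for either.

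**Working it through.** The plan gives no figure to reproduce: no detection limit, non-detect rate, effect size or sample size calculation. The only document inputs are the zero rule and the target of 50 patients (Sample Size). **Assumptions, not from the protocol:** a log-normal marker (median 1, log-SD σ of 1.0 or 1.5), correlation 0.4 between log marker and outcome, and a share f of results below the limit L. Write z = Φ⁻¹(f).

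**1. Mean.** With zeros, the expected mean is exp(σ²/2)·Φ(σ − z), so the ratio to the true mean is Φ(σ − z).

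| f | z | σ = 1.0 | σ = 1.5 |
|---|---|---|---|
| 30% | −0.524 | Φ(1.524) = 0.936, −6% | Φ(2.024) = 0.979, −2% |
| 50% | 0 | Φ(1.000) = 0.841, −16% | Φ(1.500) = 0.933, −7% |
| 70% | 0.524 | Φ(0.476) = 0.683, −32% | Φ(0.976) = 0.835, −16% |

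Simulation at n = 50, σ = 1 (4,000 runs) agrees: 1.66 to 1.55, 1.65 to 1.39, and 1.65 to 1.13. The median is unchanged at 30% and is about 0 at 70%.

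**2. Change.** Suppose a marker moves from a non-detect with true value u (0 ≤ u < L) to a detected value v ≥ L. The true change is v − u and the recorded change is v, which is at least L. The error is u, which can be almost all of L. A move between two non-detects is recorded as 0. The fold change v/0 is undefined.

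**3. Log scale, marker as predictor.** Since log(0) is minus infinity, a substitute kL is needed. With s = z + ln k, the coded log value h has

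- Cov(h, g) = (1 − f) − φ(z)·ln k, where g is the true log value
- E(h) = s·f + φ(z)
- E(h²) = s²·f + z·φ(z) + (1 − f)
- slope = 0.4·Cov(h, g)/Var(h)

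At f = 0.30, z = −0.524 and φ(z) = 0.348:

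- k = 0.5: s = −1.218, Cov = 0.700 + 0.241 = 0.941, Var = 0.962. Slope = 0.4 × 0.941/0.962 = 0.39.
- k = 0.01: s = −5.130, Cov = 0.700 + 1.601 = 2.301, Var = 8.411 − 1.191² = 6.992. Slope = 0.4 × 2.301/6.992 = 0.13.

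The n = 50 simulation gives the same 0.39 and 0.13 (0.40 uncensored). The correlation moves less: 0.38 against 0.35. With σ = 1.5, the slope of 0.27 becomes 0.12 with k = 0.01. Limit/2 gives 0.38, 0.39, 0.42 and 0.48 at 10%, 30%, 50% and 70%, so it too fails when most values are non-detects.

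Adding 1, 0.1 or 0.01 before the log gives 0.64, 0.28 and 0.16 at 25% non-detects. Part of the first figure is only a change of scale, because log(x + 1) differs from log(x) even without non-detects.

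**4. Raw scale and ranks.** At n = 50, σ = 1, the raw correlation goes from 0.334 to 0.341 (30%), 0.332 to 0.331 (50%) and 0.329 to 0.301 (70%). Spearman correlation is the same for 0 and limit/2 (0.369 at 30%, 0.350 at 50%), because both merely tie the non-detects at the bottom. That equality holds for measured levels, not for differences taken before ranking. With L = 1, a patient going from non-detect to 1.2 changes by 1.2 under the zero rule and 0.7 under limit/2. A patient going from 2 to 3 changes by 1.0 under both, so their order flips.

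**The case against.** A reader might infer that the rule distorts every biomarker association. The documents do not support that. Markers without non-detects are untouched, rank associations of levels do not depend on the substitute, and raw-scale slopes hardly move until more than about half the values are below the limit. No log scale, added constant or dropping of non-detects is planned, and an article may leave the choice of scale to a fuller plan. Medians are already allowed.

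A reader might also infer severe attenuation if zeros are dropped before taking logs. With the marker as **outcome** and 25% non-detects, a slope of 0.50 does fall to 0.29. But the deterioration and SVR models use biomarkers mainly as **predictors**, where dropping non-detects leaves the slope nearly unbiased (0.397 against 0.40) and costs precision instead. In the outcome setting, log(x + 1) gives 0.28 with 25% non-detects, but already 0.25 with none, so that figure is mostly a scale effect.

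For the same reason, Tobit is not a general remedy. It handles a censored outcome, not a censored covariate in logistic, SVR or Aalen models. Its good recovery here (0.50 at 25%, 0.49 at 50%) was obtained on data simulated from its own model.

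These limits stand and set the scope of the point. They do not rescue the rule: it is stated without condition, means are permitted, changes are to be analysed, and no analysis is stated to be rank-based.

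**Conclusion.** The point holds in limited form. Zero is a poor unconditional substitute for markers with many non-detects. Means are biased downward (7% to 16% at half non-detects and 16% to 32% at 70%, for log-SD 1.5 and 1.0). Crossings of the limit are recorded as at least the full limit. Any log slope depends on the constant chosen (0.13 or 0.39 against 0.40 at 30%).

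These sizes rest on assumed log-normal markers and assumed non-detect rates. The log-scale part also rests on a transformation that is a likely choice for skewed concentrations but is not stated. For markers with few or no non-detects, the effect is small or nil. Severity is moderate, because this is an exploratory cohort for which the protocol says "On the basis of a sample size from similar studies describing pathophysiology, we aim at including 50 patients", with no formal sample size calculation.

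**What to change.** Replace the zero rule with a rule that depends on the marker's role:

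- **Biomarker as outcome:** treat non-detects as left-censored at the assay limit, for example with a Tobit model or, for the repeated samples, a censored mixed model.
- **Biomarker as predictor (logistic, Aalen and SVR models):** use a rank-based or censored-covariate method, or a stated substitute between 0 and the limit, such as limit/2, with a sensitivity analysis over other substitutes.
- **More than about half non-detects:** analyse the marker as detectable versus not.
- **Reporting:** give the percentage below the limit for each marker.

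No new data are needed. The cost is a short paragraph in the plan, somewhat more analysis work and, for the censored models, a distributional assumption that should be checked. Censored-covariate methods take more effort than a simple substitute, which is why the substitute with a sensitivity analysis is offered as an alternative.
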